### 2.6. Sample Size

In this study, the 6-month recurrence rate was used as the basis for sample size estimation. Combined with our previous research and the literature, the six-month recurrence rates of AR treated with MYN and mometasone furoate aqueous nasal spray were approximately 50% and 75% [27], respectively. Using 5% as the superiority margin, an acceptable alpha of 2.5% (one-tailed), and an acceptable beta of 20%, 86 participants were required in each group. To allow for a 10% loss to follow-up, we will recruit 190 subjects in total.

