#### 2.10.2. Primary Outcomes

The primary outcome is the six-month recurrence rate of AR after intervention withdrawalFollow-up: subjects will enter the follow-up period after withdrawal of medications. Once a relapse occurs, the patient's recurrence time will be recorded, and the follow-up ends. Otherwise, the follow-up will continue until six months after drug withdrawal.Definition of recurrence/relapse: when the RCAT score ≤21 during follow-up, the patient will be considered in a relapse stateDefinition of six-month recurrence rate: six-month recurrence rate = number of recurrent AR patients in six months/total number of patients × 100%The RCAT has sufficient reliability, validity, and responsiveness and is a simple patient self-assessment scale [29]. RCAT can be used to assess a patient's rhinitis control status in clinical practice [30]. During the treatment stage, we will collect the RCAT scale online once a week, and during the follow-up stage, we will collect the RCAT scale online every two weeks.

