#### 2.10.3. Secondary Outcomes

The secondary outcomes are the one-month recurrence rate of AR, the RCAT score, the duration of follow-up (days), the duration of medication (days), the nasal endoscopic results, the visual analog scale (VAS), the total nasal symptom score (TNSS), the rhinoconjunctivitis quality of life questionnaire (RQLQ), the total ocular symptom score (TOSS), the TCM syndrome score of spleen Qi deficiency and lung Qi deficiency, and the classification and determination scale of constitution of TCM.(1)$$\begin{array}{c} \text{Definition of one}-\text{month recurrence rate}=\frac{\text{Number of recurrent AR patients in one month}}{\text{Total number of patients}}\times 100\%. \end{array}$$

All of these will be recorded before/after the intervention and when relapse occurs on the paper version of the CRF.

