### 2.12. Statistical Methods

All analyses will be based on the intention-to-treat (ITT) principle. Missing data will be reduced to a minimum. For data loss caused by subject drop-out, data from the previous measurement will be carried forward. The frequency, percentages, means and standard deviations, medians, and quartiles will be calculated for descriptive analysis. Intergroup comparisons of continuous variables will be performed using the *t*-test or Mann–Whitney *U* test. Categorical variables will be compared using Pearson *χ*^2^ tests or Fisher exact tests. Time-to-event outcomes will be analyzed using the Kaplan–Meier method and Cox proportional hazard models. Two-tailed *p* < 0.05 will be considered statistically significant for all analyses. All statistical analyses will be conducted using SPSS version 25.0 for Windows (IBM Corporation, Armonk, NY, USA).

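### As written, the six-month recurrence comparison makes no use of baseline RCAT; the unadjusted test is valid, but adjusting could gain some precision at almost no cost

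*Protocol article*

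**What the plan says.** Section 2.10.2 defines the primary outcome as a proportion: "six-month recurrence rate = number of recurrent AR patients in six months/total number of patients". The event is an RCAT score of 21 or less at any follow-up assessment.

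Section 2.12 assigns methods by type of variable. For a proportion it says "Categorical variables will be compared using Pearson *χ*^2^ tests or Fisher exact tests". For times to an event it says "Time-to-event outcomes will be analyzed using the Kaplan–Meier method and Cox proportional hazard models". It names no covariate for either, and it does not single out a test for the primary outcome.

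Section 2.10.3 lists the RCAT score among the secondary measures and then says "All of these will be recorded before/after the intervention and when relapse occurs on the paper version of the CRF". Section 2.8 stratifies the randomisation by the three centres.

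Section 2.6 assumes recurrence of 50% on the test spray and 75% on mometasone, and continues: "Using 5% as the superiority margin, an acceptable alpha of 2.5% (one-tailed), and an acceptable beta of 20%, 86 participants were required in each group".

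**The concern.** The event is a cut-off on a patient-reported scale, and the pre-treatment value of that same scale is a natural candidate predictor. It is measured before treatment, so adjusting for it adds no post-randomisation bias. A 2×2 test leaves any variation it explains in the error term. It also leaves any chance difference in baseline RCAT between the arms in the estimated risk difference. Standardising a logistic model over baseline RCAT targets the same marginal risk difference, with a smaller standard error if the score is prognostic.

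The sample size gives almost exactly the 80% power aimed for, so there is little slack against the margin. The trial is also open-label. A covariate chosen after the data are seen would be open to the charge of being data-driven, so the choice is better fixed beforehand.

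**Working it through.** **Inputs.** From section 2.6: recurrence 50% and 75%, margin 5 points, one-sided 2.5%, power 80%, 86 per arm. From section 2.12: two-sided 5%, no margin mentioned. Not in the documents, hence assumed over a range: r, the within-arm correlation between baseline RCAT and recurrence.

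**1. Reproducing the plan's sample size.**

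n per arm = [0.75×0.25 + 0.50×0.50] × (1.960 + 0.842)² / (0.25 − 0.05)² = 0.4375 × 7.849 / 0.04 = 85.85, rounded up to 86. This agrees with "86 participants were required in each group".

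**2. Unadjusted power and precision at 86 per arm.**

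- SE = √(0.4375/86) = 0.0713.
- Power against the margin = Φ(0.20/0.0713 − 1.96) = 80.1%.
- 95% CI half-width = 1.96 × 0.0713 = 14.0 points.

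**3. Adjusted power against the margin.** The model is P_a(X) = expit(α_a + βX), with X the standardised baseline score and each α_a set so that the arm's overall risk is 50% or 75%. For n per arm, the large-sample variance of the standardised risk difference is

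{E[P₁(1−P₁)] + E[P₀(1−P₀)] + Var(P₁−P₀)/2} / n.

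| r in each arm (control, test) | Variance reduction | Power against margin, 86 per arm | n per arm for 80% power | 95% CI half-width (points) |
|---|---|---|---|---|
| 0, 0 | 0% | 80.1% | 86 | 14.0 |
| 0.09, 0.10 | 1% | 80.4% | 86 | 13.9 |
| 0.17, 0.19 | 3% | 81.4% | 84 | 13.8 |
| 0.24, 0.28 | 7% | 82.8% | 80 | 13.5 |
| 0.31, 0.35 | 11% | 84.5% | 77 | 13.2 |
| 0.37, 0.41 | 16% | 86.3% | 73 | 12.8 |

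The shortcut of multiplying the variance by (1 − r²) agrees. At r = 0.2, Φ(0.20/√(0.4375×0.96/86) − 1.96) = 81.6%. At r = 0.4, with 0.84 in place of 0.96, it is 86.4%.

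**4. The same question for a test without a margin.** The pooled event rate at 50% v 75% is 0.625. Two-sided Pearson power is Φ([0.25 − 1.96×√(2×0.625×0.375/86)]/0.0713) = Φ(1.476) = 93.0%. In simulation (4,000 replicates, 86 per arm), Pearson was compared with the treatment test from a logistic model adjusted for the baseline score:

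| r, about | 50% v 75%: Pearson, adjusted | 55% v 75%: Pearson, adjusted |
|---|---|---|
| 0 | 93.4%, 93.3% | 79.3%, 79.1% |
| 0.2 | 93.2%, 94.1% | 78.8%, 80.2% |
| 0.25 | 92.8%, 94.2% | 79.4%, 81.7% |
| 0.4 | 92.5%, 96.1% | 78.1%, 85.0% |

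The gain at the planned rates is about 1 to 4 points. If the true rates are 55% and 75%, it is about 1 to 7 points.

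**5. Type I error and the cost if the score is useless.** With 75% in both arms, two-sided type I error was 4.4% to 5.5% for Pearson and 4.4% to 4.9% for the adjusted test. A separate simulation of the standardised risk difference against the margin (3,000 replicates) gave one-sided error of 2.5% to 3.0%, against 2.6% to 2.8% unadjusted. At r = 0, power was 78.8% adjusted and 79.2% unadjusted, a difference of 0.4 points.

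All adjusted figures are for one baseline covariate. The effect of adding centre was not computed.

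**The case against.** The strongest reply is that nothing here is wrong. An unadjusted comparison of two proportions is valid in a randomised trial, matches the sizing and delivers the planned power. That stands in full. A reader might infer that the trial is underpowered, or that power is certainly being lost. The documents support neither, because the loss exists only to the extent that baseline RCAT predicts recurrence.

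A second reply is that section 2.12 is a short paragraph in a condensed article. It does not name the primary test, does not rule out adjusted analyses and lists Cox models, which can carry covariates. This also stands. It would go too far to say that the protocol forbids adjustment, or that a missing covariate list is a defect. What remains is that the only tests stated for a proportion take no covariate, and that this can be improved.

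A third reply concerns the likely size of r. Entry is limited to persistent, moderate-severe disease. Withdrawal normally follows two weeks with RCAT above 21. The event may come up to nine months after baseline (three months of treatment plus six of follow-up). Each feature may weaken the link. The direction is not certain either: the denominator is all patients, and the article does not say how patients who never reach control are counted. One might be tempted to quote a gain of about 10 points at r = 0.5, but nothing in the documents supports a correlation that large.

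Finally, baseline RCAT collection is likely rather than certain. The sentence in section 2.10.3 also covers items that cannot exist before treatment, such as recurrence. Section 2.10.1 does not list RCAT at baseline, section 2.9.3 describes weekly RCAT once treatment has begun, and the timeline table is not shown.

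**Conclusion.** The point holds as an efficiency suggestion. As section 2.12 is written, the binary six-month comparison makes no use of a baseline score that the trial appears to collect. For assumed correlations of 0.1 to 0.4, adjustment would lower the variance by about 1% to 16%, add about 0 to 6 points to the 80.1% power against the margin, and narrow the 95% CI half-width from 14.0 points to between 13.9 and 12.8. Without a margin, the gain at the planned rates is about 1 to 4 points on about 93%. If baseline RCAT is not prognostic, there is no gain and a loss of a fraction of a point.

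These figures rest on the plan's event rates, 86 analysed per arm, a roughly normal baseline score and an assumed correlation. The case for the change is that its cost is very small, not that its benefit is known to be large.

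**What to change.** In section 2.12, pre-specify the primary comparison as follows:

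- Fit a logistic model for six-month recurrence with treatment, pre-treatment RCAT as a continuous covariate, and centre, because centre is the randomisation stratum.
- Standardise to the marginal risk difference, with a robust standard error and a 95% confidence interval. This is the scale on which section 2.6 sized the trial.
- Keep the unadjusted chi-square test as a supporting analysis.
- Use the same baseline covariates in the Cox model for time to recurrence.
- Do not adjust for RCAT at withdrawal, which is measured after randomisation.

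Confirm in the visit schedule that RCAT is recorded before the first dose.

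The cost is a sentence or two in the statistical methods and some extra code for the standardised estimate. If the schedule confirms the baseline score, no further data, visits or patients are needed. The downside is a model-based primary estimate in place of a 2×2 table, with a possible loss of a fraction of a point of power if the score proves not to be prognostic. The change should be made before outcome data by arm are seen.

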### 2.13. Strategies to Improve Adherence to Interventions and Promote Participant Retention and Complete Follow-Up

High compliance consists of adequate communication with the subjects, providing appropriate reward mechanisms and establishing a good doctor-patient relationship. During recruitment, the subjects will receive extensive information about the study. Subjects will receive free treatment and examinations and will be correspondingly compensated after each follow-up visit to our clinic. Researchers will emphasize the importance and benefits of completing the follow-up. Because AR is a recurrent disease, subjects may relapse after a period of remission. This study will follow the whole process of AR of subjects from onset to clinical control to recurrence and provide corresponding clinical advice to the subjects in case of recurrence. Moreover, a medication compliance index will be used to evaluate the subjects' compliance.

### 2.14. Data Management and Monitoring

Data entry and management are the responsibility of dedicated data managers. Scales will be collected through CRF. Before recruitment, all researchers worked together to formulate the standard operating procedure (SOP) of this study. According to the SOP, the principal investigator (PI) regularly holds training meetings for all researchers to guarantee interobserver consistency to ensure the reliability of clinical data. A quality control monitor will confirm that the records and reports of all research data are correct and complete and ensure that they are consistent with the original data throughout the study.

### 2.15. Criteria for Adverse Event Reporting and Discontinuing or Modifying the Allocated Interventions

Subjects may refuse to participate in the study or withdraw from the study at any time during the study without affecting their medical treatment and benefits. If a patient is uncooperative, the investigators can also end the patient's participation in this study. The investigators will make a follow-up appointment (by phone, e-mail, and message), contact the subject if possible, inquire about the reason for withdrawing, the time of last medication, and complete as many assessment items as possible. If any adverse event (AE) occurs during the trial, the responsible investigator should take the necessary measures to provide treatment. Any serious adverse events (SAEs) will be reported within 24 h to the sponsor and the ethics committee. The manifestation, severity, onset time, duration, and prognosis of the adverse events will be observed and recorded in detail. A committee of medical experts will determine whether it is related to the treatment. In the case of AE and injuries caused by diagnostic tests or research drugs, effective measures should be taken to ensure the safety of the subjects. Moreover, the research team will pay the related treatment costs and the corresponding economic compensation according to China Good Clinical Practice Guideline.

### 2.16. Confidentiality

All study-related information (basic information, data, laboratory reports, forms, and informed consent) will be identified by the random sequence number and stored by the PI in lockers or encrypted on designated computers. Serum, nasal lavage fluid, and nasal mucosa samples from this study will be placed in a locked refrigerator. Data containing personal identifiers will be destroyed three years after the end of the trial.

### 2.17. Ethics and Dissemination

This study will be conducted under the guidance of the Helsinki Declaration and has been approved by the ethics committees of all medical centers (Table 4) (S2). If it is necessary to modify the protocol, we will submit the modified protocol to the funder and the ethics committees of this study. After obtaining the approval of the funder and the ethics committees, we will revise the protocol and record it on the Chinese Clinical Trial Registry. The complete protocol for this study is available on the official website of the Chinese Clinical Trial Registry [31] (registration number: ChiCTR2100047053). The results will be presented to subjects by telephone after the follow-up period. Moreover, the results will be reported according to the Consolidated Standards of Reporting Trials (CONSORT) in medical journals and presented at academic conferences to benefit researchers, clinicians, and patients.

## 3. Discussion

Mometasone furoate aqueous nasal spray will be administered to the control group in this study. Intranasal corticosteroids (INCs) are first-line treatments for persistent or moderate-severe AR patients [32]. INCs are effective for the four significant classic symptoms of AR and ocular symptoms of AR [1]. INCs are more effective than H1-antihistamines and leukotriene receptor antagonists, especially for nasal obstruction [32]. The mechanism of action is related to the local anti-inflammatory effect of nasal mucosal cells. Second-generation INCs further minimize systemic bioavailability (<1%) compared with first-generation INCs and oral corticosteroids [33], thereby limiting systemic effects on AR. Some studies have shown that AR is a local reaction of systemic inflammation and systemic immune inflammation of multiple organs and systems caused by allergen invasion [34]. The existence of systemic inflammation will keep the body in a sensitized state, and it is easily restimulated when encountering allergens, resulting in recurrence. Therefore, the insufficient systemic efficacy of INCs also limits their efficacy in controlling recurrences.

In contrast, the comprehensive regulation of multitargets and multilinks is a characteristic of TCM [35]. The TCM theory holds that “the lung opens into the nasal.” On the one hand, nasal disease is the external manifestation of lung status. On the other hand, the nose communicates directly with the lung, and drug administration from the nose can directly affect the lung. It should be emphasized that the concept of “lung” in TCM is not the concept of the anatomical lung but a high generalization of a series of “lung” functions. Moreover, maintaining the body's defense function is one of the lungs' primary functions. Therefore, through nasal administration, the medication can directly affect the lung, and the filled lung Qi can regulate the defense function of the nasal cavity and the whole body; in this way, the recurrence of AR can be controlled. Although INCs and MYN are both administered intranasally and can control the symptoms of AR, their underlying action logic is different, and we believe that this difference is the key to controlling recurrences. Furthermore, compared to other kinds of nasal corticosteroids, the mometasone furoate aqueous nasal spray is safer and can be administered to children above three years. Given the reasons mentioned above, we chose the mometasone furoate aqueous nasal spray as the intervention in the control group.

Subjects between 18 and 65 will be enrolled in this study. All of the herbs in MYN are herbs with high safety. Moreover, MYN has been used in the clinic for more than 20 years, and the efficacy and safety of MYN have been approved [18–23]. The safety of the mometasone furoate aqueous nasal spray is internationally recognized and can be administered to children above three years old [1,33]. This study will recruit AR subjects aged 18–65 years because most Chinese children under 18 years, especially those aged 13–18 years, are junior and senior high school students who live on campus, and it is difficult to require timely follow-up visits during the follow-up period. Therefore, people in this age group were not included in the study. The elderly population (over 65 years) has a distinct clinical presentation, including an increased incidence of rhinorrhea symptoms and a low prevalence of AR [36]. The management of elderly AR patients may differ from that of the general adult population [32]. Therefore, this age group was not included in the study.

According to previous research [21], symptom scores returned to normal on the 14th day of MYN administration in animal models. The short-term treatment course of nasal corticosteroids for AR is 2–12 weeks [37]. This study will only enroll patients with persistent and moderate-severe AR, and the short-term treatment course of nasal corticosteroids for moderate-severe AR is four weeks. Therefore, the shortest treatment course should not be less than four weeks, and the longest treatment should not be more than three months. Subjects should continue the treatment for two weeks until the clinical control standard has reached a stable effective state.

The RCAT scale was used to determine whether patients experienced AR relapse. There is no “gold standard” for evaluating the efficacy of AR [38]. The RCAT is one of the most widely validated rhinitis control scales, and its reliability, validity, and responsiveness have been widely validated [38]. The RCAT is a simple, self-rating scale that allows patients to assess their AR control at home [30] and helps gauge the success of therapeutic interventions repeatedly over a long period [29, 39]. Therefore, in this study, the RCAT will be regularly sent to subjects, and the RCAT score will be recorded to reflect the rhinitis control status and relapse status of subjects. In this study, the six-month recurrence rate of AR after drug withdrawal will be the primary outcome, reflecting the long-term efficacy of MYN in controlling relapses. The one-month recurrence rate will be used to reflect the short-term efficacy of MYN in controlling AR relapses. This will directly reflect the speed of relapse through the duration of follow-up. The longer the follow-up is, the slower it recurs; conversely, the shorter the follow-up is, the faster it recurs. In fact, more meaningful data would have been collected if follow-up had been extended. However, considering that the loss rate of subjects will increase with the extension of follow-up time, prolonged follow-up time may have many uncertainties affecting the accuracy of the study results. Therefore, the maximum follow-up time of this study is 6 months. If the results of this experiment show that MYN can control the recurrence of AR, the follow-up period will be extended to observe the efficacy of prolonged control of recurrence in future studies.

Limitations: this study also has limitations. For example, MYN is a nasal spray made from pure Chinese medicine. It is brown and has a light herbal odor, while the mometasone furoate aqueous nasal spray is colorless and odorless, so it is difficult to blind subjects to treatment. Therefore, this study adopts an open-label design, but this may cause bias in evaluating the efficacy of relapse control. Nasal endoscopy examination will be conducted on subjects before and after interventions to objectively reflect the efficacy of the interventions and minimize the influence of psychological effects on subjects in an open-label design. Efforts to make MYN colorless and odorless are ongoing.

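### Raw duration of follow-up is read as speed of relapse, so a relapse-free drop-out looks like a fast relapse

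*Protocol article*

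**What the plan says.** Section 2.10.3 lists among the secondary outcomes "the duration of follow-up (days), the duration of medication (days"), giving a unit but no event and no rule for incomplete observation.

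The Discussion (Section 3) then says what follow-up duration is for: "This will directly reflect the speed of relapse through the duration of follow-up". It continues: "The longer the follow-up is, the slower it recurs; conversely, the shorter the follow-up is, the faster it recurs". No exception is made for patients who leave.

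Section 2.10.2 ends follow-up at relapse, defined as RCAT at or below 21, and adds: "Otherwise, the follow-up will continue until six months after drug withdrawal". Other sections foresee a third ending:
- Section 2.6: "To allow for a 10% loss to follow-up, we will recruit 190 subjects in total".
- Section 2.15 lets subjects withdraw whenever they wish.
- Section 3 gives as a reason for stopping at six months: "considering that the loss rate of subjects will increase with the extension of follow-up time".

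Section 2.12 offers two routes. One is: "Time-to-event outcomes will be analyzed using the Kaplan–Meier method and Cox proportional hazard models". The other begins "Intergroup comparisons of continuous variables will be performed using the" and names the t-test or the Mann–Whitney U test. Neither sentence names an outcome. The same section carries the previous measurement forward for drop-outs.

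**The concern.** Length of follow-up measures time to relapse only in patients who relapse. In patients still controlled at six months it is a lower bound set by the calendar, and in drop-outs a lower bound set by the day they left. Reading every short follow-up as a fast recurrence turns that last group into early relapsers.

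The protocol then treats one patient in opposite ways. Someone lost while still controlled has a last RCAT above 21. Carried forward, that value makes the patient non-recurrent for the primary outcome, while the short follow-up reads as rapid recurrence for the secondary one.

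At stake is a secondary outcome offered as the direct measure of how fast patients relapse. If loss differs between arms, a difference in retention can pass for a difference in relapse, or hide one. Subjects and researchers are unblinded, so unequal loss is plausible.

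**Working it through.** **Two patients side by side.** Take day 28 after withdrawal as an example.

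| Patient | Primary outcome | Raw follow-up days | Discussion's reading | Censored analysis |
|---|---|---|---|---|
| Relapses on day 28 | recurrent | 28 | fast relapse | event at 28 |
| Leaves on day 28, last RCAT above 21 | not recurrent (carried forward) | 28 | fast relapse | censored at last RCAT |

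Raw days cannot tell the two apart.

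**Arm size.** Section 2.6 gives recurrence of 75% and 50%, a 5% margin, one-sided 2.5% and 80% power:

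n = (0.75×0.25 + 0.50×0.50) × (1.960 + 0.842)² / (0.25 − 0.05)² = 0.4375 × 7.85 / 0.04 ≈ 85.9, so 86 per group.

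86 × 1.1 = 94.6, so 95 per arm and 190 in total. The protocol's figures reproduce, and 95 per arm is used below.

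**Size of the bias when the arms relapse equally.** Assumptions: six months = 182 days; exponential relapse reaching 60% by day 182 in both arms; exponential drop-out in which a share d would leave by day 182 if none relapsed first. Mean raw follow-up is then

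E(d) = 182 × [1 − 0.4(1 − d)] / [−ln 0.4 − ln(1 − d)].

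| d | 0% | 5% | 10% | 15% | 20% | 30% |
|---|---|---|---|---|---|---|
| Mean days | 119.2 | 116.6 | 114.0 | 111.3 | 108.6 | 102.9 |

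For d = 20%: 182 × 0.68 / (0.9163 + 0.2231) = 123.76 / 1.1394 = 108.6.

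False-positive rates of a Mann–Whitney test on raw days, two-sided 5%, 95 per arm, from repeated simulation runs (2,000 and 4,000 trials per scenario among them):

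| Loss, arm A vs arm B | Spurious gap in mean days | False positives |
|---|---|---|
| 10% vs 10% | 0 | 4.2–5.2% |
| 15% vs 5% | 116.6 − 111.3 = 5.3 | 7.9–8.2% |
| 20% vs 5% | 116.6 − 108.6 = 8.0 | 14.0–14.9% |
| 30% vs 10% | 114.0 − 102.9 = 11.1 | 21.8–22.0% |

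**Does censoring cure it?** A second model (1,500 trials per scenario) detects relapse every 14 days, as the two-weekly RCAT would, and spreads drop-out uniformly over six months.

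| Scenario | t-test, raw days | Mann–Whitney, raw days | Log-rank, censored |
|---|---|---|---|
| Equal relapse 62.5%, loss 10% vs 10% | 6.0% | 5.7% | 4.9% |
| Equal relapse 62.5%, loss 20% vs 0% | 18.8% | 19.9% | 4.7% |
| Planning rates 50% vs 75%, loss 10% each (power) | 88.5% | 89.9% | 95.5% |
| Planning rates, loss 20% MYN vs 0% control (power) | 53.5% | 54.3% | 95.4% |

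Censoring keeps the error rate near 5%, and has more power even when loss is balanced.

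**Effect on the planned difference.** Without loss, expected follow-up is 182 × 0.50 / ln 2 = 131.3 days for MYN and 182 × 0.75 / ln 4 = 98.5 for control, a gap of 32.8 days. Under the second model's drop-out the gap is 30.8 days with 10% loss in each arm, 21.2 with 20% in MYN only, and 40.5 with 20% in control only.

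**The case against.** The strongest reply is that the protocol already contains the right analysis. Section 2.10.2 gives an origin (drug withdrawal), an event (RCAT at or below 21), a recorded recurrence time and an end at six months, and Section 2.12 plans Kaplan–Meier and Cox. Time to relapse is the natural candidate for those methods, since most other outcomes are proportions, scores or examination results. The Discussion sentence is informal rationale, and a condensed article may leave the assignment of methods and the censoring rule to a fuller document.

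Much of this stands. A reader might infer that the trial will run a t-test or Mann–Whitney test on raw days; the text does not establish that. Nor is the absence of a censoring rule, by itself, the point. What remains is the stated interpretation. It equates short follow-up with fast relapse in a protocol that expects drop-outs, and no unseen document makes that correct.

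Three stronger readings fail:
- **Medication days as speed of control, with early leavers counted as quick successes.** No section interprets medication duration this way. It is listed in days, and Sections 2.9.1 and 2.9.2 give only its stopping rule and its four-week and three-month bounds.
- **Retention rather than efficacy drives the outcome.** At the planning rates the gap is 32.8 days without loss and 30.8 with equal 10% loss, so efficacy dominates.
- **The many patients sitting at the six-month limit are a defect.** At the planning rates 25–50% would be there, but without drop-out a comparison of capped days is valid: simulated error was about 5%.

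**Conclusion.** The concern holds for duration of follow-up. The Discussion's reading is wrong for any patient who leaves without relapsing, and it sets this outcome against the primary outcome's handling of the same patient. The time-to-event methods that would resolve it are planned but not tied to it.

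The numerical consequence depends on retention. With equal 10% loss, the only loss figure in the protocol, false-positive inflation is negligible (about 5%). It grows to about 8%, 14% and 22% at 15% versus 5%, 20% versus 5% and 30% versus 10%. These figures assume exponential relapse and drop-out, the stated arm-specific losses, and a test on raw days. The losses are potential ones: at 20% versus 5%, the shares actually lost before relapse would be 0.2231/1.1394 × 0.68 = 13.3% and 0.0513/0.9676 × 0.62 = 3.3%.

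For duration of medication only a precaution is warranted: medication can end at control, at the maximum or at withdrawal, and a bare count of days does not distinguish them. The primary outcome and the sample size are unaffected. This should be corrected before analysis, at the weight of a secondary outcome.

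**What to change.** 1. In Section 2.10.3, replace duration of follow-up with time from drug withdrawal to relapse. The event is RCAT at or below 21; drop-outs are censored at their last RCAT and all others at six months.
2. In Section 2.12, state that the Kaplan–Meier and Cox analysis already planned applies to this outcome, in place of a t-test or Mann–Whitney test on raw days.
3. In the Discussion, rewrite the two sentences on follow-up duration so that speed of relapse is read from time to relapse with censoring.
4. For duration of medication, either report it descriptively or separate patients who stopped on reaching control from those who reached the maximum and those who withdrew, so that early stopping is not counted as control.

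The cost is wording. Recurrence times are already to be recorded and RCAT is already collected every two weeks in follow-up, so no new data, visits or subjects are needed, and no treatment rule changes.
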